# The SmartNTx-study: a prospective, randomized controlled trial to investigate additional interventional telemedical management versus standard aftercare in kidney transplant recipients

**DOI:** 10.3389/fneph.2025.1591962

**Published:** 2025-06-19

**Keywords:** kidney transplantation, aftercare, patient empowerment, APP, randomized controlled trial (RCT)

## Abstract

**Background:**

Regular follow-up care after kidney transplantation is performed in transplant centers together with local nephrologist practices in Germany. Patients after kidney transplantation have to fulfill many tasks and manage their disease, follow a complex therapeutic regimen, communicate with the transplant center and home nephrologists, and coordinate doctor appointments. It has been shown that mHealth solutions such as mobile phone applications (apps) can support patients in their self-management. However, stand-alone apps have limitations and ideally, the mHealth solutions are embedded in a holistic treatment approach, including healthcare professionals.

**Methods:**

We will conduct a 1-year, prospective, randomized, 2-armed, parallel group multicenter trial in three German Kidney Transplant Centers (KTCs) to demonstrate that additional and continuous interventional telemedical management will improve health after kidney transplantation in patients of all ages. Therefore, a composite endpoint of seven key outcome variables [fewer hospitalizations, shorter length of hospitalization, less development of *de novo* donor-specific antibody (DSA), better medication adherence, lower tacrolimus intra-patient variability, better blood pressure control, and better renal function after kidney transplantation]was defined. All the patients will receive the same routine post-transplant aftercare. The patients in the interventional arm will receive additional predefined telemedical management, including regular telemedicine visits and automatic bidirectional data transfer (e.g., vital signs, wellbeing, medication plan, and laboratory data together with a chat option) between the patient at home and the KTC through a certified smartphone app. If necessary, a home nephrologist can be included in the automatic data transfer. In the interventional arm, the iBox score will be used to better detect patients at risk for early graft failure and drug-drug interactions will be regularly checked with certified software.

**Discussion:**

The study aims to prolong patient and graft survival through additional telemedical services in order to reduce avoidable hospitalizations, improve treatment of co-morbidities, and improve adherence through patient empowerment, which should result in lower health care costs, and better quality of life of patients after kidney transplantation.

**Clinical Trial Registration:**

ClinicalTrials.gov, identifier NCT05897047.

## Introduction

End-stage renal disease (ESRD) and kidney replacement therapies are linked to high morbidity and mortality (1). Compared to dialysis, kidney transplantation (KTx) offers the best survival, quality of life (QoL), and lower healthcare costs for patients with ESRD. According to current guidelines for immunosuppressive therapy, tacrolimus (a calcineurin inhibitor) combined with anti-IL-2 receptor antibodies (e.g., basiliximab), mycophenolate (e.g., Mycophenolate mofetil (MMF) or Enteric coated Mycophenolate sodium (EC-MPS)), and steroids, has significantly improved renal transplantation outcomes, particularly in reducing acute rejection rates to below 15% (2–5). As rejection is most common in the first year, early prevention is crucial for optimal outcomes, as rejections are linked to graft loss, prolonged hospitalizations, and over-immunosuppression. In addition, over-immunosuppression can increase infection risks, such as urinary tract infections (UTI), BK virus (BKV), and cytomegalovirus (CMV) (6–13). Thus, an adequate initial rejection prophylaxis is the key to optimal long-term outcomes in KTx.

Immunosuppressive drugs can also elevate cardiovascular risks, such as hypertension and diabetes, necessitating personalized treatment (14–19). The leading cause of graft loss remains death with a functioning graft, followed by T-cell mediated rejection (TCMR) and chronic antibody-mediated rejection (ABMR), often linked to non-adherence (20). Holistic care addressing adherence and cardiovascular risks through structured aftercare, adherence training, and sports therapy has been shown to improve graft survival (8, 21). This holistic approach, which systematically addresses non-adherence and cardiovascular risks in a structured aftercare program with adherence training and sports therapy, can lead to an improvement in graft survival, as demonstrated in our recent publication (22).

Yet, cardiovascular death remains the most common cause of premature death, with hypertension as the major modifiable risk factor (23–25). Despite improvements, blood pressure control and cardiovascular risk factor management after KTx remain suboptimal (26). In the multicenter “FAVORIT” trial, 44% of patients on antihypertensive medication had blood pressure readings above 140/90 mmHg (27). Furthermore, 24-hour blood pressure monitoring has shown better correlations with end-organ damage than office measurements, and the 2018/2023 ESC/ESH Guidelines recommend a target of <140/90 mmHg for patients over 65 (18, 28). The treatment goal here should not differ from that of the dialysis population or patients with advanced CKD. A target of less than 135/90 mmHg seems a reasonable compromise to avoid graft hypoperfusion and cardiovascular complications (18). For children, blood pressure targets should match age-related norms, with hypertension defined as values above the 95th percentile + 5 mmHg (29). German normal blood pressure percentiles for children and adolescents are given in the KIGGS-Report (30).

Since renal function alone has limitations in predicting graft loss, *Loupy* et al. developed an AI-based model called iBox to predict graft loss better in kidney transplant recipients (KTRs). The model integrates data such as transplant time, renal function, proteinuria, donor-specific antibodies (DSAs), and histopathology, achieving excellent predictive accuracy (C index 0.81). It has been validated across European and US cohorts and is proposed as an early surrogate endpoint for clinical trials (31–33). The iBox is an integrative, accurate, and readily implementable risk prediction evaluation for kidney allograft failure, which shows generalizability across centers worldwide and common clinical scenarios. The iBox risk prediction model is used as a valid and early surrogate endpoint in clinical trials.

We and others have shown that non-adherence is another common problem after kidney transplantation and thus has been called the 5th vital sign (34–36). There are many tools to evaluate medical adherence, including the level to which a disease (e.g., blood pressure) is controlled, assessment of drug levels, and self-assessment by the patient or the physician in charge, amongst others. In general, structured self-assessments are considered to be very useful and provide an important cornerstone for assessing adherence. The Basel Assessment of Adherence to Immunosuppressive Medication Scale (BAASIS^©^) has been developed in particular to detect immunosuppressive medication adherence and is increasingly used (37–41) Evidence suggests that tacrolimus intra-patient variability (IPV) is a strong prognostic factor for long-term outcomes, with high IPV linked to poor results. Reducing IPV requires addressing non-adherence through patient education and minimizing drug-drug interactions (42, 43). In general, drug-drug interactions are a frequent problem in patients on complex medication schemes. Unsurprisingly, they may cause severe side effects and hospitalizations (42, 44–46). In tacrolimus-treated organ transplant recipients, the inadvertent application of enzyme-inducing drugs may cause acute transplant rejections, while inhibition of drug metabolism may cause severe toxicity in nephrotoxicity (47). Thus, regular and easy assessment of drug-drug interactions, e.g., by a certified software solution, may be useful and may help to reduce tacrolimus IPV and drug-associated complications.

UTIs are common after transplantation, with approximately 74% of patients affected in the first year post-transplant, decreasing to 35% in the second year and 21% by the fourth year (48, 49). Severe UTIs are a frequent cause of hospitalization and Abbott et al. found that late UTIs increased the risk of graft failure 2.35-fold (50). Moreover, recipients who develop septicemia are at higher risk of death due to cardiovascular events compared to recipients without infections. Pellè et al. confirmed that late UTIs were associated with worse long-term patient survival and are an independent risk factor for worse outcomes (49). Late UTIs are also associated with higher mortality from cardiovascular causes, and recurrent UTIs in the first year post-transplant predict worse graft function at 3 years (HR 2.2; 95% CI 1.3–3.5) (51).

In conclusion, long-term success after transplantation depends on multiple factors. A holistic approach with regular follow-up from experienced physicians is vital. Patients face challenges managing complex regimens, coordinating with healthcare providers, and maintaining adherence. mHealth applications offer a promising solution to support self-management and empower patients, with studies demonstrating the utility of eHealth and telemedicine (52–54).

In this randomized trial, we test whether a comprehensive eHealth intervention in combination with a dedicated team will have a positive impact on adherence, blood pressure control, hospitalizations, and transplant outcomes.

## Methods and analysis

In this 1-year, prospective, randomized, 2-armed, parallel group multicenter trial in three German Kidney Transplant Centers (KTCs), we want to demonstrate that additional and continuous interventional telemedical management will lead to a better composite endpoint of seven key outcome variables. The key outcome variables are fewer hospitalizations, shorter length of hospitalization, less development of *de novo* DSA, better medication adherence, lower tacrolimus intra-patient variability, better blood pressure control, and better renal function after kidney transplantation. **Figure 1** depicts the study design.

**Figure 1 f1:**
[figure not shown]
Study design.

All patients will receive the same routine post-transplant aftercare. Patients in the interventional arm will receive predefined additional telemedical management, including regular telemedicine visits and automatic data transfer (vital signs, wellbeing, medication plan, laboratory data, and chat) between the patient at home and a KTC through a certified smartphone application. Furthermore, the home nephrologists of patients in the interventional arm will be invited to participate in the automatic data transfer of key variables (such as vital signs and laboratory data) with the KTC. A separate telemedicine team will constantly review the incoming data according to a predefined protocol and eventually contact the patient and/or the home nephrologist to start appropriate interventions. For patients in the interventional arm, physicians will use the certified iBox score based on the “iBox” algorithm (Predict4Health, Paris, France) to better detect patients at risk for early graft failure. In the interventional arm, drug-drug interactions will be regularly checked with the help of certified software (ID Medics^®^, GmbH & Co. KGaA, Berlin, Germany).

It has been previously demonstrated that additional telemedical care may affect a variety of important key outcome variables for long-term success after kidney transplantation (22, 52, 53). In our trial, we chose a composite endpoint of such variables as the primary outcome. Under the assumption of a small to medium effect size of Cohen’s d = 0,31, we calculated that 192 patients per group (including a 20% drop-out rate) are needed to show a difference between groups. Thus, the study population will consist of approximately 384 KTRs, irrespective of age. They will undergo central web-based randomized placement in one of the two treatment groups in a 1:1 ratio. Because expected key outcomes (e.g., hospitalization rate and adherence) may differ according to the age of participants and the time post-transplant, we will stratify them at randomization not only by KTC, but also according to patients’ age: 18–65 years and >65 years. Randomization of children was stratified only by age and not by KTC because of the low expected number of children per KTC (< 12 years, 12 to 18 years).

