### Randomization

Randomization will be performed using a predefined variable block randomization scheme, stratified by the participating centers and the age of the participant. Due to low expected patient numbers in the age groups of < 12 years and 12 to 18 years, patients in these age groups will be randomly stratified by age, but not by KTC. The randomization scheme will be generated and reviewed by the study biostatistician and quality assurance staff and locked by them after approval. The investigation sites will assign eligible patients through an interactive internet-based computer system (IWRS) once a patient has satisfied the requirements to be included in the study. The IWRS randomization tool is part of the eCRF (Secutrial^®^, interActive Systems, Berlin, Germany). After screening for eligibility and assignment of the individual PID, each patient can only be assigned once to one of the treatment arms. Using the web-based tool will make it impossible for the study personnel to predict the assignment. The sites will record the time of randomization. Treatment in the assigned group starts in the first year after the kidney transplantation and ends in month 12 after randomization.

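### Time since transplantation is given as a reason to stratify but is not a stratification factor, and the stated adjustment rule covers it only if imbalance is seen

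*Protocol article*

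**What the plan says.** The sentence on stratification in Methods and analysis (text after Figure 1) gives two reasons for stratifying and then turns to the factors: key outcomes "may differ according to the age of participants and the time post-transplant, we will stratify them at randomization not only by KTC, but also according". Two adult age bands complete the list, divided at 65 years. For children it adds: "Randomization of children was stratified only by age and not by KTC". The Randomization section describes the scheme as "stratified by the participating centers and the age of the participant". No section makes time since transplantation a stratification factor.

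The Inclusion criteria admit patients up to 12 months after transplantation, and the Randomization section says: "Treatment in the assigned group starts in the first year after the kidney transplantation and ends in month 12 after randomization". The Statistical analysis plan section allows potential confounders into the regression models if the two groups turn out to differ on relevant variables. It does not name time since transplantation.

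**The concern.** A reader of the stratification sentence could believe that time since transplantation was dealt with at randomization. It was not, and the article itself shows why it may matter:

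- The 12-month observation window runs from post-transplant months 0–12 for the earliest entrants to months 12–24 for the latest.
- The Introduction describes urinary tract infection "with approximately 74% of patients affected in the first year post-transplant, decreasing to 35% in the second year" and calls severe infections a common reason for admission. Two of the seven primary indicators concern unplanned hospitalization.
- Table 1 thins routine visits from weekly to one every 4–6 weeks, so the background care to which telemedicine is added also changes with entry time.

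If entry time predicts the 0–7 score, an unadjusted comparison leaves that variation in the error term and is exposed to whatever imbalance chance produces. A rule that admits the covariate only after imbalance is seen makes the model depend on the data. It also gives up the precision gain when the arms happen to look balanced.

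**Working it through.** **Inputs from the article.** 192 per group, 20% drop-out, d = 0.31, 1:1 allocation, entry at 0–12 months, 12 months of follow-up.

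**Assumptions.** Entry is uniform over 0–12 months. Tests are two-sided at 0.05. The correlation ρ between entry time and the primary score is not given, so a range is shown.

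**The plan's own figure.** Alpha and power are not stated, so 192 per group cannot be reproduced from the article alone. With two-sided 0.05 and 80% power, d = 0.31 needs 164 per group, which becomes 205 (164/0.8) or 197 (164 × 1.2) after drop-out. The point does not depend on this; 192 is used only as the arm size.

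**Strata.** Adults: 3 centres × 2 age bands = 6. Children: 2 age bands. Total 8, none using time since transplantation.

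**Span.** Entry at 0–12 months plus 12 months of follow-up covers post-transplant months 0–24. Month-12 assessments fall at post-transplant months 12–24.

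**Chance imbalance in entry time**
- SD of entry time = 12/√12 = 3.46 months.
- SE of the standardized difference = √(2/192) = 0.102, so the 95% limit is 1.96 × 0.102 = 0.20 SD.
- In months: 0.20 × 3.46 ≈ 0.7.
- With 154 completers per arm (192 × 0.8 = 153.6): 0.22 SD, or about 0.8 month.

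**Shift in the unadjusted estimate at that limit (192 per arm), ρ × 0.20**

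| ρ | shift (SD of score) | share of d = 0.31 |
|---|---|---|
| 0.1 | 0.02 | 6% |
| 0.3 | 0.06 | 19% |
| 0.5 | 0.10 | 32% |

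**Precision.** With adjustment the residual SD is √(1 − ρ²), and power is Φ(0.31/√(2(1 − ρ²)/154) − 1.96). Unadjusted, this is 77.6%. Adjusted, it is 78.1% at ρ = 0.1, 79.3% at 0.2, 81.4% at 0.3 and 88.1% at 0.5.

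**Validity.** In 20,000 simulated null trials with ρ = 0.3 and 192 per arm, the unadjusted t-test rejected in 4.97%. The nominal level is kept.

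**Urinary tract infection as an anchor.** If risk falls linearly with entry time from 74% to 35%, the slope is 39/12 = 3.25 points per month, and a two-SE imbalance (2 × 0.102 × 3.46 = 0.7 month) moves expected risk by about 2.3 points. Infection is not one of the seven indicators. If every infection failed exactly one indicator, the score would shift by 0.023. With an assumed score SD of 1.2–1.5, that is 0.015–0.02 SD. The between-patient SD of risk is 3.46 × 3.25 = 11.3 points, so the implied ρ is 0.113/1.5 to 0.113/1.2, about 0.08–0.09. Failing both hospitalization indicators would double this.

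**The case against.** The strongest reply is that the scheme is consistent: both sections give centre and age for adults and age alone for children, and only the stated reason goes further. That is right. The two descriptions of the scheme do not conflict, and the article says outcomes may differ by time since transplantation, not that this factor is decisive.

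A reader might also infer that the factor is left uncontrolled and that the treatment effect is biased. The article does not support this. Allocation at 1:1 balances entry time in expectation, the type I error holds, and the article leaves room for adjustment.

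Nor can the 2.3 points be read as an effect on the endpoint. They concern infection, while the indicators count only unplanned admissions of at least 24 hours. By that anchor alone ρ is near 0.1 and the gain is small. Other indicators could add to it, but nothing in the article supports a particular larger value.

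It might further be said that the average effect cannot be assigned to the first or second post-transplant year. That follows from the eligibility window, a deliberate choice, and stratifying would not change it.

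Finally, covariate lists commonly belong to the analysis plan, which is not shown and may already include this one. That would be a full answer if the article were silent. It is not: it states a rule triggered by observed imbalance, and that rule can be judged as written.

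**Conclusion.** The point holds in a limited form. The article's reason for stratifying names a factor that its scheme does not use, and its stated adjustment rule is a weak substitute for a variable the trial itself expects to be prognostic. The consequence is lost precision and possible chance imbalance; the primary test stays valid.

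Over ρ of 0.1 to 0.3, a 95%-limit imbalance moves the estimate by 0.02 to 0.06 SD, and adjustment adds about 0.5 to 4 percentage points of power (78.1 and 81.4 against 77.6). These sizes rest on uniform entry, two-sided 0.05, 154 completers per arm for power, and a correlation the article does not give. The effect is modest, but the remedy costs almost nothing.

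**What to change.** Recruitment finished in April 2025, so the strata are fixed. Two changes remain open before analysis, with the last patient out expected on 30 April 2026:

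1. Correct the sentence in Methods and analysis to say that time since transplantation was not a stratification factor.
2. Prespecify months from transplantation to randomization, as a continuous variable, as a fixed covariate in the primary model next to the actual stratification factors, regardless of observed balance. If the full analysis plan already does this, align the article with it.

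The treatment effect by entry time may be reported as an exploratory subgroup, but this is optional.

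The cost is a sentence in each document and one degree of freedom. No new data are needed, because the Death and Graft loss sections already count survival from the date of transplantation.

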### Method of assigning patients to the treatment groups

At the baseline visit, study personnel will register the patients, who will sign the ICF, in the database and will assign a unique patient identification number (PID number). The PID number will only identify the patient’s records. The investigator will keep a master patient list on which the PID number and the full name, address, and telephone number of each patient are listed.

For data collection, five study visits at the KTC are scheduled (months 0, 3, 6, 9, and 12). For the determination of tacrolimus trough level, two additional time points will be used (months 7.5 and 9.5). In addition, medication adherence, quality of life, and treatment satisfaction will be assessed by validated questionnaires.

### Group 1 – routine aftercare

The routine aftercare (control group) will be scheduled according to the current standard of care, which depends on the time after transplantation, medical condition, and other individual factors. Standard immunosuppression will be applied according to international recommendations (55). The prophylaxis and treatment of infections will follow the current standard of care as outlined in recent guidelines (56–61), e.g., *Pneumocystis jirovecii* pneumonia (PjP) prophylaxis, CMV prophylaxis according to guidelines, or regular post-transplant BKV monitoring according to guidelines (3). Screenings for antibodies against human leukocyte antigen (HLA) will be performed once within the first 3 months (HLA screening results prior to randomization of the patient can be used if these are not older than 6 months) and after 1 year and in the case of suspected rejection (62). Overall medical treatment of the KTRs will be performed according to KDIGO guidelines (3). A kidney biopsy should be performed in patients with suspected rejection and classified according to the most recent Banff criteria (63). An integral part of the current routine aftercare is regular home nephrologist and KTC visits in adults, where data are captured in an electronic health record (EHR) (64). **Table 1** provides the proposed schedule for post-transplant aftercare. The proposed schedule will be adapted to the patient´s individual needs.

**Table 1 T1:** Routine visits after transplantation.

Time of visit	Time point
Month 1	1x per week after discharge (either at KTC or by home nephrologist)
Month 2	1x per week (either at KTC or by home nephrologist)
Month 3	1x per 2 weeks (either at KTC or by home nephrologist)
Months 4 to 6	1x per 3 weeks (either at KTC or by home nephrologist)
Months 6 to 12	1x per month (either at KTC or by home nephrologist)
After month 12	1x per 4–6 weeks (either at KTC or by home nephrologist)

